## 4. Trial Population

### 4.1 Screening data

For each study centre, data will be collected on number of subjects screened, number eligible, number enrolled and reasons for screen failures. This data will be reported in the clinical study report (CSR) by study centre.

### 4.2 Eligibility

Inclusion and exclusion criteria are defined in the study protocol.

### 4.3 Recruitment

A CONSORT patient flow diagram will be constructed following the CONSORT 2010 standards (<http://www.consort-statement.org/consort-2010>) to illustrate number of subjects screened, enrolled and randomized.

### 4.4 Baseline patient characteristics

Evaluations of the baseline characteristics will be based on the FAS. They will be presented in a descriptive summary table by treatment group—continuous variables as mean and standard deviation or median and quartiles, and categorical variables as absolute and relative frequencies. No statistical comparisons of patient characteristics at baseline will be performed.

Maternal baseline characteristics to be summarized include

- Age
- Ethnicity
- In Utero antenatal transfer
- Administration of antenatal steroids (incidence and number of doses)
- Spontaneous labour
- Preterm premature rupture of membranes (evidence of and duration of),
- Intra-partum antibiotic use
- Mode of delivery and
- Indication for mode of delivery
- Administration of regional anaesthesia (e.g. spinal, epidural)
- Administration of general anaesthesia

Infant baseline characteristics to be summarized include

- Best estimate of gestational age (GA)
- Method for determining GA
- Gender
- Multiplicity
- Birth weight

|         |                                           |               |
|---------|-------------------------------------------|---------------|
| UCD CRC | SAP for the POPART trial                  |               |
| UCD CRC | Template: Statistical Analysis Plan (SAP) | Version: 1.0  |
|         |                                           | Page 11 of 19 |

- Apgar scores (1, 5, 10 min)
- resuscitation at delivery

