### OROPHARYNGEAL SURFACTANT GROUP

Infants randomised to oropharyngeal surfactant will receive a dose of surfactant (Curosurf, Chiesi Farmaceutici, Parma, Italy) (18) immediately after birth, ideally before the cord is clamped e.g. 60 seconds. If it is given after the cord is clamped it will be given once the infant is placed on the resuscitaire. It will be given within 5 minutes of birth in all cases.

The surfactant will be warmed prior to being drawn up in a sterile syringe as per manufacturer's recommendation. This will be done by opening the mouth gently and administering the surfactant as a single bolus into the oropharynx using a syringe without a needle attached. This will be done as soon as possible after delivery, ideally before the umbilical cord has been clamped.

The dosing recommendations for initial treatment with Curosurf when given by endotracheal tube are:

- 200mg/kg for established RDS
- 100 – 200mg/kg for prophylaxis

One or two further doses of 100mg/kg Curosurf may be given to infants who have persistent respiratory distress despite treatment with surfactant (maximum recommended dose 400mg/kg).

The timing or dosage of ET surfactant will not be affected by initial oropharyngeal surfactant. If an infant is felt to need ET surfactant following initial oropharyngeal administration, then they will receive the standard initial dose of 200mg/kg via ETT.

Infants in our study will not be weighed prior to enrolment. The 50th centile for birth weight (BW) for boys and girls according to gestational age (GA) is shown below

| GA (weeks) | Gr s BW (kg) | Boys BW (kg) |
|------------|--------------|--------------|
| 23         | 0.550        | 0.600        |
| 24         | 0.650        | 0.700        |
| 25         | 0.775        | 0.800        |
| 26         | 0.850        | 0.900        |
| 27         | 0.975        | 1.050        |
| 28         | 1.100        | 1.150        |

In our study, infants < 26 weeks will receive a full 120mg vial of Curosurf. We estimate that this will provide dosing in the therapeutic range as indicated below:

| GA (weeks) | Gr s BW (kg) | Dose (mg/kg) | Boys BW (kg) | Dose (mg/kg) |
|------------|--------------|--------------|--------------|--------------|
| 23         | 0.550        | 218          | 0.600        | 200          |
| 24         | 0.650        | 185          | 0.700        | 171          |

|    |       |     |       |     |
|----|-------|-----|-------|-----|

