#### 11.3.6 Method of assigning Subjects to treatment groups

Infants will be randomised to receive oropharyngeal surfactant or CPAP (which is the standard of care) in a 1:1 ratio using variable block randomisation, with block sizes of 4, 6 and 8. Randomisation will be stratified by participating centre. The more prematurely an infant is born, the higher their risk is of being

intubated for respiratory support in the first 120 hours of life (primary outcome). It is important to ensure balance in the risk of reaching the primary outcome between the two treatment arms at study entry; thus we will also stratify the randomisation by gestational age (<26 weeks and 26-28 weeks inclusive).

Infants of multiple gestations will be randomised as individuals.

A computer-generated randomisation schedule will be prepared by an independent statistician who will not be involved with subsequent data analysis or interpretation. The schedule will be stored securely on a password protected computer. The randomization list will be numbered using sequential 6-digit randomization codes (e.g. NMH001, NMH001,...). Each group assignment – “OROPHARYNGEAL SURFACTANT” or “CONTROL” – will be written on a card that will be labelled with its corresponding 6-digit randomisation code (e.g. NMH001). Each card will be folded in half and placed in an opaque sealed envelope that will be labelled with the same 6-digit randomisation code. The envelopes will then be placed in sequential order (e.g. NMH001, NMH002, NMH003...) in separate boxes for the two gestational age strata for each centre. At each centre, the boxes containing the envelopes will be stored securely in the neonatal intensive care unit (NICU), as the clinical team will need to have access to the randomisation envelopes. An envelope from the appropriate box (<26 weeks or 26–28 weeks) will be opened immediately before birth.

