### 14.4 Demographic and baseline disease characteristics

Demographic and baseline data will be summarized for each treatment group. The date of birth, gender and race of the infant will be recorded. Gestation, multiplicity, birth weight and resuscitation at delivery, including Apgar scores, will be documented. Maternal age will be recorded. We will also record administration of antenatal steroids, preterm premature rupture of membranes (evidence of and duration of), intra-partum antibiotic use, the mode of delivery and indication for mode of delivery.

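### SAP 4.4 treats Apgar scores and delivery-room resuscitation as baseline items with no effect estimate, although all are post-randomisation and the 5- and 10-minute scores fall at or after the bolus

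*Combined protocol and SAP*

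**What the plan says.** SAP 4.4 (Baseline patient characteristics) includes the Apgar scores at 1, 5 and 10 minutes and "resuscitation at delivery" in its list of infant baseline items. Of the baseline items as a whole it says "They will be presented in a descriptive summary table by treatment group" and "No statistical comparisons of patient characteristics at baseline will be performed". Protocol 14.4 (Demographic and baseline disease characteristics) groups the same items with the baseline data: "Gestation, multiplicity, birth weight and resuscitation at delivery, including Apgar scores, will be documented". Neither document defines the components of resuscitation at delivery.

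On timing, protocol 11.3.6 says that the allocation envelope "will be opened immediately before birth". The description of the oropharyngeal surfactant group in protocol 11.1 puts the bolus straight after birth, ideally before cord clamping, with 60 seconds as the example, and adds: "It will be given within 5 minutes of birth in all cases".

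Protocol 10.3 and SAP 1.3 make delivery-room intubation, number of intubation attempts, chest compressions and adrenaline secondary endpoints. Apgar scores are not on either list.

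**The concern.** A baseline table describes infants before treatment could have affected them. Readers take differences between its columns as chance, and leaving them untested is correct for that reason. Neither holds for a measurement made after allocation, and still less for one made after the drug.

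What is at stake is early tolerability of an off-label route. Protocol 9.2 names bradycardia and desaturation among the side effects of the product, and the product table in protocol 13.3 adds apnoea. Apgar scores and minor resuscitation come from the minutes in which such a reaction would appear, and they are recorded in both arms. Under SAP 4.4, a lower 5-minute score in the surfactant arm would appear in the baseline table with no estimate or interval, under a label implying that it preceded treatment.

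**Working it through.** **1. Timing.** Take birth as time zero. Allocation is revealed just before zero. The bolus falls between 0 and 5 minutes, with a target of about 1 minute.

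| Item | Relative to allocation | Relative to bolus |
|---|---|---|
| 1-minute Apgar | after | before or after |
| 5-minute Apgar | after | at or after |
| 10-minute Apgar | after | after, by at least 10 − 5 = 5 minutes |
| Resuscitation at delivery | after | undefined; may span the bolus |

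Protocol 11.3.4 agrees with this order. It places the day-of-birth assessments, including chest compressions and adrenaline, after randomisation.

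**2. What is compared between arms.**
- Delivery-room intubation, chest compressions and adrenaline: relative risk, 95% interval and two-sided Z test in all randomised infants (SAP 5.1.1).
- Delivery-room intubation attempts: analysed as a numeric endpoint, among infants intubated there (SAP 5.1.1).
- Apgar scores: descriptive table by arm only. No section of either document plans an effect estimate.
- Resuscitation measures outside the endpoints above, if the item contains any: descriptive table by arm only.

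**3. The adverse-event route.** Protocol 13.3 says that bradycardia, apnoea and desaturation need no regular reporting in the case report form. Protocol 14.6 says that events after the bolus, with bradycardia and desaturation as examples, will be documented. The two sections conflict and must be reconciled. If 13.3 governs, the tables in SAP 5.4 and the safety board's review under protocol 13.5 may miss a short-lived reaction, and the delivery-room measures carry more of the safety information.

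**4. The plan's sample size.** Inputs from protocol 14.2: 46% against 28%, two-sided 5%, 80% power. With pooled variance under the null hypothesis,

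n per arm = [1.96·√(2 × 0.37 × 0.63) + 0.842·√(0.46 × 0.54 + 0.28 × 0.72)]² / 0.18² = 112 after rounding up, or 224 in total.

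224 / 0.9 = 249, which the protocol states as 250. The figure reproduces, and nothing in this point changes it.

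**5. What an estimate would add.** The documents give no delivery-room event rates, so every rate here is an assumption. Take 250 / 2 = 125 infants per arm.

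With the same rate p in both arms, the 95% half-width for the difference is 1.96·√(2p(1 − p)/125). The third column is the smallest increase detectable with 80% power.

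| Assumed control rate | Half-width (points) | Detectable increase (points) |
|---|---|---|
| 5% | 5.4 | 10.8 |
| 10% | 7.4 | 13.2 |
| 20% | 9.9 | 15.9 |
| 30% | 11.4 | 17.2 |
| 40% | 12.1 | 17.7 |

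Two illustrations with Wald intervals:
- 75% against 60%: 15 ± 1.96·√(0.75 × 0.25/125 + 0.60 × 0.40/125) gives 15 points, 95% CI 3.5 to 26.5, p = 0.011.
- 70% against 60%: 10 points, 95% CI −1.8 to 21.8, p = 0.097.

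SAP 4.4 would produce neither interval.

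**The case against.** The strongest reply is that serious acute harm is already covered. Three major delivery-room events are tested between arms, and intubation attempts are compared as well. The primary endpoint text in SAP 1.3 includes delivery-room intubation for persistent apnoea or bradycardia, so a reaction severe enough to need a tube would reach a tested endpoint. This stands. A reader might infer that delivery-room resuscitation is not compared at all, and that is not so. The gap is Apgar scores and any lesser measures. Since the resuscitation item is undefined, it may contain nothing beyond the tested endpoints.

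Baseline items are also shown by arm, so a difference would be visible and a crude one could be worked out from the table. That is right, and it limits the harm. It does not supply a planned estimate or interval, or correct the label.

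The word baseline may simply mean the day-of-birth visit. Protocol 11.3.4 uses it that way, and chest compressions recorded there are still analysed as outcomes. That explains how the items came to be listed. But SAP 4.4 then applies to them a rule suited only to pre-treatment variables.

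Three further inferences fail:
- **Protocol 14.4 also bars comparison.** It does not; only SAP 4.4 does.
- **Adjusted analyses are distorted.** Neither Apgar nor resuscitation is among the covariates in SAP 5.1.1 or 5.1.2.
- **Imputation is compromised.** SAP 5.3 includes the randomised arm and expressly allows procedural and outcome variables, so a post-randomisation predictor is legitimate there.

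**Conclusion.** The point holds as a misclassification with a limited consequence. All the listed delivery-room items are post-randomisation. Two of the three Apgar times are at or after the bolus, and the third is indeterminate. No between-arm estimate is planned for Apgar scores, or for any resuscitation measure that is not already an endpoint. An early reaction could therefore be mistaken for a pre-treatment imbalance. A reader might go further and conclude that it would be read as chance; the documents do not support that, because the values are displayed by arm and the major events are tested.

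The conclusion on timing rests on the protocol's own window being followed. The importance of the gap depends on how protocol 13.3 and 14.6 are reconciled, and on what resuscitation at delivery contains. The rates used above, including 60%, 70% and 75%, are illustrative and carry no evidence about this trial. The sample size and the primary analysis are unaffected.

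**What to change.** In SAP 4.4, remove the three Apgar scores, and any delivery-room resuscitation measure not already an endpoint, from the baseline list. Define resuscitation at delivery and say how it relates to the existing endpoints.

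Report the removed items by randomised arm in all randomised infants as post-randomisation delivery-room safety outcomes, with differences and 95% confidence intervals, beside chest compressions and adrenaline. Note against the 1-minute score that the bolus may precede or follow it. State that none of these items may serve as a baseline adjustment covariate.

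Keep the rule against testing true baseline variables, and leave SAP 5.3 free to use these measures in imputation. Separately, reconcile protocol 13.3 with protocol 14.6 on recording bradycardia and desaturation.

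The cost of the SAP change is a few lines of wording and one table. The protocol already has these data collected in both arms, and this part needs no protocol amendment.

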#### 4.5 Adherence and protocol deviations

Administration of the intervention at delivery will be documented, along with reason for non-administration for infants allocated to receive the intervention. The end of study form will document whether infants completed the study per protocol, with reasons for early discontinuation also recorded on the CRF. Protocol deviations will be summarized in the CSR.

#### 4.6 Withdrawal/follow-up

All withdrawals and losses to follow-up will be listed with the time points and reasons (if available).

|         |                                           |               |
|---------|-------------------------------------------|---------------|
| UCD CRC | SAP for the POPART trial                  |               |
| UCD CRC | Template: Statistical Analysis Plan (SAP) | Version: 1.0  |
|         |                                           | Page 12 of 19 |

## 5. Analysis

### 5.1 Analysis methods

#### 5.1.1 Primary analysis

The primary estimand in this trial is the difference in the rates of endotracheal intubation for respiratory failure while alive within 120 hours of birth in future infants treated with prophylactic oropharyngeal surfactant compared to infants treated with the standard of care (no intervention). The primary analysis will be done on the full analysis set according to the intention-to-treat principle. For infants who died within 120 hours of randomization, the primary endpoint will be documented for the time period in which they were alive. Infants who were intubated without (or prior to) meeting the definition of respiratory failure defined in the protocol will be included, and will be considered to have met the primary endpoint in the main analysis.

#### Primary endpoint analysis

For the primary endpoint, the incidence of endotracheal intubation for respiratory failure within 120 hours of birth, the following analysis will be carried out.

- Descriptive statistics will be calculated to compare the rate of endotracheal intubation across treatment arms. Number and percentage of subjects meeting and not meeting the primary endpoint will be tabulated per treatment arm. Frequency of missing data per treatment arm will be quantified. Ratios of relative risk will be presented with 95% confidence intervals. Relative risk estimate with 95% confidence intervals (Wald Normal approximation) will be calculated by log binomial regression with treatment as a predictor variable
- A superiority hypothesis test (two-sided, two-proportion Z test) will be carried out to investigate whether the rate of endotracheal intubation differs between intervention and standard-of-care. In this analysis, infants intubated for signs of respiratory failure (whether or not they strictly met the pre-defined criteria in the protocol) will be considered to have met the primary endpoint.

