### 14.2 Determination of sample size subjects

In randomised studies, the rate of mechanical ventilation in the days after birth among preterm infants treated with CPAP alone has varied from 46– 60%. (2, 11, 19-21) Minimally invasive surfactant techniques were shown to reduce the rate of mechanical ventilation to from 46% to 28% in a cohort of infants with a gestational age between 26 and 28 weeks. (21)

Sample size for this study was calculated in G\*power, using a two-sided, two-proportion Z test. To detect a difference in the rate of endotracheal intubation for respiratory failure of 18% between treatment arms (assuming a rate of 46% in the control group and 28% in the intervention arm) with 80% power and a 5% significance level, a sample size of 224 infants would be required. To compensate for a death rate of 10% (estimated from local data, The National Maternity Hospital, Neonatal Clinical Report for 2015) before the primary outcome can be determined (i.e. at 120 hours), we will need to recruit a total of **250** infants to this study.

The National Maternity Hospital is a stand-alone university maternity hospital with a tertiary NICU to which > 150 infants < 1500g are admitted annually. We have a track record of initiating, conducting, completing, presenting and publishing investigator-led randomised controlled trials, including trials that compared delivery room interventions, (12-14) trials that had respiratory failure in the NICU as the primary outcome (15) and trials that compared investigational medicinal products (16) in preterm infants. Though the enrolment rates to our studies amongst eligible infants are consistently excellent (> 80%), we believe it will be necessary to enrol infants at multiple sites in order to enrol our planned target sample of 250 infants in a timely fashion. We have a track record enlisting the help of collaborators

nationally(16)andinternationally(14, 17)to perform our studies. We believe that with their help, we can enrol these infants in 2–3 years.

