## 1.4 Estimands

### 1.4.1 Primary estimand

The primary estimand in this trial is the difference in the rates of endotracheal intubation for respiratory failure while alive within 120 hours of birth in future infants treated with prophylactic oropharyngeal surfactant compared to infants treated with the standard of care (no intervention). Two potential intercurrent events were identified that could impact on observation of the primary endpoint: (1) death prior to 120 hours without observation of the primary endpoint and (2) intubation for respiratory failure without meeting the pre-specified criteria defined in the protocol.

| Intercurrent event                                                                     | Strategy for handling intercurrent event                                                                                                                                                                                       |
|----------------------------------------------------------------------------------------|--------------------------------------------------------------------------------------------------------------------------------------------------------------------------------------------------------------------------------|
| (1) Infants who died within 120 hours of birth without having met the primary endpoint | While alive strategy – data collected on the subjects while alive will be used to determine the primary endpoint, even if the observation period is shorter than 120 hours                                                     |
| (2) Infants intubated for respiratory failure within 120 hours of birth without        | Treatment policy strategy – subjects will be considered to have met the primary endpoint if they are intubated for respiratory failure within 120 hours of life (regardless of whether or not the protocol definition was met. |

|         |                          |  |
|---------|--------------------------|--|
| UCD CRC | SAP for the POPART trial |  |
|---------|--------------------------|--|

|         |                                           |              |              |
|---------|-------------------------------------------|--------------|--------------|
| UCD CRC | Template: Statistical Analysis Plan (SAP) | Version: 1.0 |              |
|         |                                           |              | Page 7 of 19 |

|                                                |  |

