### 5.1.2 Sensitivity analyses

Sensitivity analysis will be conducted for the primary endpoint as follows.

- The sensitivity of the estimated intervention effect to measured covariates of interest (centre, gestational age, birth weight, gender, mode of delivery (vaginal versus caesarean birth) and antenatal corticosteroid treatment) will be evaluated by regression modelling. Generalized estimating equations will be fitted to the primary endpoint, with predictors including treatment and the above covariates. The relative risk of occurrence of the primary endpoint will be calculated for intervention vs placebo after adjustment

|         |                                           |               |
|---------|-------------------------------------------|---------------|
| UCD CRC | SAP for the POPART trial                  |               |
| UCD CRC | Template: Statistical Analysis Plan (SAP) | Version: 1.0  |
|         |                                           | Page 14 of 19 |

for the above covariates using binomial generalized estimating equations with the small sample Kauermann and Carroll correction of the variance estimator used to calculate 95% confidence intervals around the relative risk.

- A competing risks model will be applied to investigate the effect of the intervention on the primary endpoint, adjusting for other outcomes that may impact on observation of the primary endpoint (e.g. death occurring before 120 hours of birth or intubation prior to 120 hours without meeting the criteria for respiratory failure defined in the protocol), should these competing risks occur.
- For infants intubated without meeting the pre-defined criteria for respiratory depression in the protocol, a sensitivity analysis will be conducted by assuming these infants would not have met the primary endpoint (i.e. as negative on the primary endpoint). Analysis will proceed as for the main analysis of the primary endpoint.
- A per protocol analysis of the primary endpoint will be conducted to determine whether the treatment effect is sensitive to protocol deviations. Analysis will proceed as for the main analysis of the primary endpoint.

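### The primary test and relative risk leave out the randomisation strata, so the test is conservative to the extent that those strata are prognostic, and no confidence interval is planned for the rate difference that is the declared estimand.

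*Combined protocol and SAP*

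**What the plan says.** **Randomisation.** Protocol 11.3.6 stratifies by centre. It then says that prematurity raises the risk of the primary outcome, "thus we will also stratify the randomisation by gestational age (<26 weeks and 26-28 weeks inclusive").

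**Primary test.** SAP 5.1.1, under Primary endpoint analysis: "A superiority hypothesis test (two-sided, two-proportion Z test) will be carried out to investigate whether the rate of endotracheal intubation differs". SAP 2.2 and protocol 14.5.1 name the same test, and none of the three mentions strata.

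**Primary effect measure.** A relative risk whose estimate and interval "will be calculated by log binomial regression with treatment as a predictor variable".

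**Adjustment.** SAP 5.1.2 lists centre and gestational age among the covariates of a sensitivity analysis: "Generalized estimating equations will be fitted to the primary endpoint, with predictors including treatment and the above covariates". Its output is again a relative risk. SAP 5.1.3 adds interaction models for both factors.

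**Estimand.** SAP 1.4.1: "The primary estimand in this trial is the difference in the rates of endotracheal intubation". SAP 5.1.1 repeats it. SAP 5.6 sets the quality-control tolerance for the primary confidence limits at 0.5 percentage points.

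**Sample size.** Protocol 14.2 computes it "using a two-sided, two-proportion Z test", "assuming a rate of 46% in the control group and 28% in the intervention arm". It finds that "with 80% power and a 5% significance level, a sample size of 224 infants would be required", raised to 250 for deaths.

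**The concern.** Balancing a prognostic factor by design removes its contribution to the sampling variance of the treatment comparison. A test that uses the marginal variance puts that contribution back. Its standard error is then larger than the true one, P values are too large and intervals too wide. The protocol itself says that gestational age is prognostic, so this is expected here; only its size is open.

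The second issue needs no assumption about rates. The estimand, the design difference of 18 points and the quality-control tolerance are all on the risk-difference scale. The only primary effect estimate given an interval is on the ratio scale. A reader of the trial report would find no interval for the quantity that the plan declares to be its target.

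**Working it through.** **1. The plan's own figure.** Inputs from protocol 14.2: 46% and 28% (mean 37%), two-sided 5%, 80% power.

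n per arm = [1.960·√(2·0.37·0.63) + 0.842·√(0.46·0.54 + 0.28·0.72)]² / 0.18² = 111.8, so 112 per arm and **224** in total, an exact match. 224/0.9 = 248.9, consistent with 250.

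SAP 1.4.1 keeps early deaths in the analysis, so about 250 infants are analysed. The Z test then has 84.3% power if the strata are not prognostic, against 80.1% at 224.

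**2. Effect on the standard error.** Let w be the share <26 weeks and g the gap in control rates between strata. The between-stratum variance is B = w(1−w)g². The total under the null at 46% is T = 0.46·0.54 = 0.2484. Stratified allocation removes B, so the true SE is √(1−B/T) times the SE that the Z test uses. The true type I error is 2·[1 − Φ(1.960/√(1−B/T))].

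Worked case, w = 0.30 and g = 0.34 (control rates about 70% and 36%):
- B = 0.21·0.1156 = 0.0243, and B/T = 0.098.
- SE ratio = √0.902 = 0.950. Effective critical value = 1.960/0.950 = 2.063. Type I error = 3.9%.

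**3. Power in the same case.** Assume a common odds ratio with marginal rates held at 46% and 28%. The treated stratum rates are then 49.2% and 18.9%.
- True SE = √[(0.2241 + 0.1823)/125] = 0.0570, from the within-stratum variances of the two arms.
- Z test: SE used = √(2·0.37·0.63/125) = 0.0611. Power = Φ[(0.18 − 1.960·0.0611)/0.0570] = 85.5%.
- Stratified test: SE used = √(2·0.2114/125) = 0.0582. Power = Φ[(0.18 − 1.960·0.0582)/0.0570] = 87.6%.

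A simulation of stratified blocks of 4, 6 and 8 with 6 assumed centres agrees: type I error 3.9% for the Z test and 4.8% for the Cochran-Mantel-Haenszel (CMH) test, power 85.4% and 87.4%.

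**4. Range, w = 0.30, N = 250.**

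| Gap between strata (points) | B/T | Type I error, formula | Type I error, simulated | Power gain, formula (points) | Power gain, simulated (points) |
|---|---|---|---|---|---|
| 0 | 0 | 5.0% | about 5% | 0 | about 0 |
| 10 | 0.008 | 4.9% | about 5% | 0.2 | about 0 |
| 20 | 0.034 | 4.6% | about 4.5% | 0.7 | about 0.5 |
| 34 | 0.098 | 3.9% | 3.8-3.9% | 2.2 | about 2 |
| 49 | 0.203 | 2.8% | 2.4-2.8% | 4.4 | about 5 |

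At gaps of 0-10 points, CMH over gestational age by centre was level with the Z test or up to 0.8 points below it in simulation, where the Monte Carlo error was about 0.6 points. Centre effects widen the difference. With 9 assumed centres, centre SD 0.5 on the logit scale and a 30-point gap, type I error was 3.7% unadjusted and 4.7% stratified, and power 84.6% and 87.0%.

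**5. The missing interval.** At the design rates with 125 per arm, the unadjusted risk difference is −18.0 points with SE √[(0.2484 + 0.2016)/125] = 0.060, so the 95% CI is −29.8 to −6.2. The planned output is RR 0.28/0.46 = 0.61, 95% CI 0.43 to 0.85. Only the second interval is specified.

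**The case against.** The strongest reply is that test and sample size agree. The 224 was computed for the same unadjusted Z test, so a reader who infers that the trial is underpowered, or that its planned power is lost, goes further than the documents allow. The loss exists only relative to a stratified test. Nor is there any false-positive risk, since the error is conservative. All of this stands.

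The size is also undocumented. With a gap of 10 points or less there is nothing to gain, and the benefit depends on a gap that the plan does not state. This stands too, and is why the range starts at zero.

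The strata are not ignored everywhere: both are covariates in the planned adjusted relative risk, and both have interaction models. That is correct. It does not change the test that decides the trial, and the adjusted result is again a ratio.

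A reader might also infer that the estimand is never estimated. That is too strong. SAP 5.1.1 tabulates percentages per arm, so the crude difference is a subtraction, and the Z test tests that difference. What is missing is an interval for it. The percentage-point tolerance in SAP 5.6 may be loose wording for the relative-risk limits, so it is only supporting evidence.

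**Conclusion.** The point holds as one of efficiency and reporting; the validity of the test is not threatened. The primary analysis departs from the stratified design, and its standard error is too large to the extent that the strata are prognostic. Assuming 30% of infants <26 weeks and 250 analysed, type I error falls from about 5% (gap 0-10 points) to 2.4-2.8% (gap 49), and the power forgone against a stratified test rises from about 0 to about 5 points. The direction follows from the protocol's own statement about prematurity. The size rests on stratum rates, a share <26 weeks and a number of centres that the documents do not give.

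The lack of a planned confidence interval for the declared estimand is a plain inconsistency within the SAP and needs no assumption.

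**What to change.** In SAP 2.2 and 5.1.1:
- Make the primary test a Cochran-Mantel-Haenszel test stratified by gestational-age stratum and centre. Fix a numerical threshold for pooling small centres, set without sight of outcomes by arm.
- Report the Mantel-Haenszel risk difference with 95% CI as the primary estimate, and the Mantel-Haenszel relative risk with 95% CI beside it.
- Keep the crude Z test as a supportive analysis.
- In SAP 5.6, tie the percentage-point tolerance to the risk-difference interval.
- State whether the change carries over to the categorical secondary endpoints, which SAP 5.1.1 analyses in the same way as the primary.

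Record this in SAP section 6 as a change from protocol 14.5.1, dated before database lock and before the statistician is unblinded. The documents do not show whether lock has passed. If it has, keep the Z test as primary and add the stratified test and the risk-difference interval, labelled as post hoc.

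The cost is a documented departure from the primary test named in the protocol, and a little more analysis work. Centre and gestational age are already held as randomisation factors.
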